**Fig. 2 Fig2:**
[figure not shown]
Flowchart of the eight reading strategies evaluated within STREAM. Every screening examination will be evaluated based on two radiologists and one radiologist and one AI prediction. The radiologists will evaluate every screening examination with four different strategies

The two double-reading strategies will include standard double-reading with a third reader in case of discrepancy between the first two readers, and AI as one reader and a radiologist as the second reader and another radiologist as arbiter in case of discrepancies.

Twenty radiologists will evaluate 200 examinations of the first round with each of the different reading strategies. The 200 examinations will be different from the examinations used for the first reader study, where we compare reading times and user-friendliness. Cases and reading strategies will be randomised in the usual manner, with the necessary four-week wash-out period between sessions. For each interpretation, we will record the location and probability of malignancy score for each suspicious lesion, and a recall/no recall decision, in addition to reading time. We will estimate the JAFROC figure of merit [20], and the case-based AUC for each of the DBT reading strategies studied.

To compare the result of using the standard double-reading by two screening radiologists to that of using hybrid AI-human double-reading, the results of the radiologists reading mentioned above and of the computer system analysis of these 200 cases will be used. For this, first, all interpretations by one radiologist will be paired at random with those of another, to replicate blinded double-reading by two independent radiologists. The AI-based results will be dichotomised into recall/no recall using the operating point that would result in the same average recall rate as the screening radiologists in the first screening round of this trial. Sensitivity and specificity of the final screening outcomes will be the endpoint of these studies.

Once the best reading strategy has been found, all DBT examinations of the second round will be re-interpreted using it. The decision of the first evaluation by the two radiologists will be the gold standard. Wherever possible, different radiologists than the ones who did the first evaluation of the second-round reading will read the corresponding case. The readers will be informed if the second reader is another radiologist or a computer system. The recall rate, breast cancer detection rate, PPV of recall, and interpretation time will be compared to the first evaluation of the second round, allowing for a real-world evaluation in actual screening practice.

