#### Sample size calculations

Sample size calculations were done in G*Power (version 3.1.9.4. using an alpha of 0.05, a beta of 0.20, two-sided *Z*-test and an allocation ratio for the control/intervention group of 5) based on the primary outcome measure; i.e., the sum of the IC and advanced cancer (AC) rate at the seco nd round (combined endpoint) in the DBT group compared to the control group. We powered the trial to detect a reduction in the primary outcome measure of 1.3 per 1000, which reflects a difference of 36% from this combined endpoint with DM (3.6 per 1000) (see further details in Supplementary Appendix C). This requires a sample size for the intervention group in the second round of 17,275 screening examinations with DBT. Assuming 95% re-attendance, this requires 18,184 screening examinations with DBT in the first round. The sample size for the control group is five times that of the intervention group in the second round, i.e., 86,375 participants screened with DM. Again, assuming a 95% re-attendance rate, 90,693 participants are required. For practical reasons, the sample sizes for the first round were rounded off to 18,200 in the intervention group and 91,000 in the control group.

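### Replicating double reading by random pairing of readers adds small, avoidable chance variation; averaging over all reader pairs and all eligible arbiters removes it without new readings

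*Protocol article*

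**What the plan says.** All of this is in the protocol article, Data analysis, Reading strategies, in the text around Fig. 2.

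- Design: "Twenty radiologists will evaluate 200 examinations of the first round with each of the different reading strategies". Each interpretation yields "a recall/no recall decision, in addition to reading time".
- Human double reading: "standard double-reading with a third reader in case of discrepancy between the first two readers".
- Hybrid double reading: "AI as one reader and a radiologist as the second reader and another radiologist as arbiter in case of discrepancies".
- How human double reading is built from the single readings: "all interpretations by one radiologist will be paired at random with those of another, to replicate blinded double-reading by two independent radiologists".
- Endpoint of the human-human versus AI-human comparison: "Sensitivity and specificity of the final screening outcomes will be the endpoint of these studies".

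The article does not say how many times the random pairing is drawn, or whether the third reader is drawn per pair, drawn per case or averaged over.

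**The concern.** On the natural reading, all 20 radiologists read the same 200 cases, so the result of every pair with every possible third reader can be computed from decisions already recorded. Splitting 20 readers at random into pairs uses 10 of the 190 available. The resulting sensitivity and specificity carry a component that comes neither from readers nor from cases, only from the draw.

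The comparison helps choose among eight approaches. According to the article, the chosen strategy is used to re-interpret all second-round examinations, and the costs in the cost-effectiveness analysis are based on it. The Discussion adds that the reading strategy analysis cannot be redone in the funding period. If human-human and AI-human reading turn out close, a result that changes with the draw is harder to reproduce and slightly less precise than it could be.

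**Working it through.** **Plan's own figure.** The article gives no precision or power figure for the reader study, so there is none to reproduce here.

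**Step 1: combinations available.** From 20 readers who all read the same cases:
- reader pairs: 20 × 19 / 2 = 190
- standard reading, pair plus arbiter: 190 × 18 = 3,420
- hybrid reading, reader plus arbiter: 20 × 19 = 380
- one random split into disjoint pairs: 20 / 2 = 10 pairs

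**Step 2: the full average has a closed form.** Assume that the arbiter's decision is taken from that reader's own recorded recall decision. Let k of the 20 readers recall a given case.
- Standard: the outcome is the majority of three readers, so the average over all 3,420 combinations is [C(k,3) + C(k,2)(20 − k)] / C(20,3), with C(20,3) = 1,140.
- Hybrid, AI recalls: 1 − C(20 − k,2)/190.
- Hybrid, AI does not recall: C(k,2)/190.

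Example with k = 14. Standard: (364 + 91 × 6)/1,140 = 910/1,140 = 0.798. Hybrid: 1 − 15/190 = 0.921 if the AI recalls, and 91/190 = 0.479 if it does not. Averaging over the cancers gives sensitivity; one minus the average over the negatives gives specificity.

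**Step 3: why the full average cannot be worse.** Let T be the random-pairing estimate and Y the recorded readings. Then Var(T) = Var(E[T | Y]) + E[Var(T | Y)]. The full average is E[T | Y]. It has the same target, and it drops the second term.

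**Step 4: size of that second term.** The article gives no case mix, reader performance or reader agreement, so these inputs are assumed: 65 cancers and 135 negatives, single-reader sensitivity and specificity 80%, latent inter-reader correlation 0.4 to 0.75, reader threshold SD 0.2 to 0.5. The chance SD is that of one set of 10 disjoint pairs, given the readings.

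| What is drawn | Chance SD, percentage points |
|---|---|
| Pairs only, arbiter averaged out | about 0.1 to 0.35 |
| Pairs, and an arbiter for each case | about 0.5 to 0.9 |
| Pairs, and one arbiter for each pair | about 0.8 to 1.7 |
| Nothing (all 3,420 combinations) | 0 |

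**Step 5: against the error that remains.** A second model (probit with reader and case effects; 50 or 100 cancers; mean 0.8 to 1.0, reader SD 0.2 to 0.6, case SD 0.5 to 1.0; also assumed) gives a reader-and-case sampling SD of 3.0 to 5.0 points for sensitivity. For the hybrid-minus-standard difference in sensitivity it is 1.5 to 2.5 points.

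Worked case (100 cancers, mean 1.0, reader SD 0.4, case SD 1.0), where the difference has sampling SD 1.73 points:
- pairs only: (0.21/1.73)² ≈ 0.015, so 1.5% is added to the variance
- pairs and an arbiter per case: (0.72/1.73)² ≈ 0.17, so 17%
- pairs and one arbiter per pair: (0.97/1.73)² ≈ 0.31, so 31%
- all 190 pairs, but one drawn arbiter each: (0.27/1.73)² ≈ 0.024, so about 2%

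Over all scenarios of this model, pairing alone adds about 1.5 to 2.2% to the variance of the difference, and pairing plus a drawn arbiter about 14 to 42%. Most of the avoidable noise therefore comes from the choice of arbiter. Averaging over the 190 pairs alone reduces it but does not remove it.

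**The case against.** The strongest reply is that nothing here is wrong. Random pairing is unbiased, contradicts no other passage and imitates practice. The sentence does not say that the pairing is drawn once; many repeated draws would converge to the full average. The rule for the arbiter is not stated either, and an article may leave both details to the full protocol or analysis plan. All of this stands. It confines the point to a single draw or a few draws, and makes it an improvement to a stated method, not an error.

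Three stronger readings are tempting, and the documents do not support them.

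- A reader might infer that pairing by itself moves sensitivity by a point or more. It does not: that size appears only when an arbiter is also drawn at random, and no such rule is in the text.
- A reader might picture the result resting on one pair of radiologists, where the second model gives a chance SD of 3.8 to 8.4 points. The quoted sentence pairs all interpretations, so this is not the plan.
- A reader might infer that the choice of reading strategy as a whole depends on the draw. The Abstract names case-based AUC and reading time as the outcomes for the reading method, and the Reading strategies section adds the JAFROC figure of merit. None of these involves pairing. Only the sensitivity and specificity comparison of human-human with AI-human reading is touched, and the chosen strategy is then evaluated again on all second-round examinations.

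**Conclusion.** The point holds as a small gain in precision and reproducibility, limited to the human-human versus AI-human comparison. If the random pairing is done once or a few times, it adds avoidable chance variation. For one set of 10 pairs the SD is about 0.1 to 0.35 percentage points from pairing, or about 0.5 to 1.7 points if the third reader is drawn as well. There is no bias. Reader and case sampling error is larger, and no way of combining the readings removes it. The sizes rest on assumed case mix, performance and agreement. The counts (190, 3,420 and 380) rest only on all 20 readers reading the same 200 cases.

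**What to change.** Replace the random pairing by full averaging:

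- Standard double reading: average over all 190 reader pairs, with each of the 18 remaining readers as arbiter for discordant cases (3,420 combinations).
- AI-human reading: average over all 20 readers, with each of the 19 others as arbiter (380 combinations).
- Confidence interval for the difference: use a method that respects shared readers and cases, such as a bootstrap that resamples both. The combinations are not independent (each reader is in 19 of the 190 pairs) and must not be counted as separate observations.

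State also that the arbiter's decision is taken from that reader's recorded recall decision, if that is what is intended. The cost is a few lines of code and a sentence or two in the plan. No additional readings are needed, and neither the target of estimation nor the conduct of the trial changes.

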## Data analysis

### Statistical analyses

The IC rate will be defined as the number of cancers, both in situ and invasive, diagnosed clinically (i.e., outside of screening) after a negative DBT in the first, second, and third year after the first screening round of the trial per 1000 screens (considering the longer screening interval). The AC rate will be defined as the number of tumours stage II or higher (TNM classification [17]) diagnosed after recall in the second screening round of the trial per 1000 screens. Data on screen-detected cancers (SDC) and IC, as well as their characteristics (e.g., stage and grade), will be obtained through linkage with the Netherlands Cancer Registry and the Dutch nationwide pathology databank for the intervention as well as the control group.

Secondary outcome measures including participation rate (i.e., percentage of participants in DBT or DM screening of the population invited), recall rate (i.e., number of women recalled for further examination per 1000 women screened), detection rate (i.e., number of women with SDC per 1000 women screened), and positive predictive value (i.e., percentage of women with SDC of women recalled) will be calculated for both screening rounds separately. The recall rate in the first round is expected to be higher due to the first-round effect of a more sensitive screening test, the learning effect for the radiologists, and the absence of prior DBT screens to compare to [18, 19]. The recall rate of the second round will estimate the long-term recall rate for DBT screening. The detection rate will be calculated for invasive and in situ cancers, overall and for cancer stage II or higher. Screening outcomes of both rounds will be stratified by breast density, as assessed by automated methods by Volpara (Mātakina Technology) and Quantra (Hologic).

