### Reading strategies

Multiple commercially available AI software solutions will be evaluated using all the data from the first round of the intervention arm. The software aims to detect malignancies in DBT images, highlight their location, and give a case-based and lesion-based score of probabilities of breast cancer. In agreement with the software vendors, the software description and the results will be reported anonymously. First, case-based probability of malignancy will be used to build recall rate/cancer detection rate curves and calculate the area under the receiver operating characteristics curve (AUC). All AI solutions with an AUC within 0.05 of the best-performing system will be used for the subsequent observer study.

With it or them, we will perform reader study sessions with ten screening radiologists to compare reading times with a dataset of 200 examinations. The dataset will be assembled from first-round cases and will include both cancer and negative cases (negative biopsies after recall and not-recalled cases verified by an expert panel). At the end of each session, the radiologists will complete a short questionnaire on the user-friendliness of each AI system. This subjective evaluation will be used in case the objective criteria of detection performance and reading time result in more than one computer system within the non-inferiority margin. The final chosen AI system will be the single one used in the evaluation of the interpretation strategies.

Four interpretation strategies for individual reading of the cases by a screening radiologist will be evaluated, combined with two different methods to achieve the double-reading of all cases, for a total of eight approaches for interpretation (Fig. 2), as follows:Standard: Acquisition of four views (CC and MLO) of DBT + the corresponding four SM images (Hologic). Interpretation using all images, with the DBT images displayed as stacks of slices with 1 mm separation.Single view DBT (MLO) + SM (MLO): Same as #1 but with interpretation of only the MLO views.Slabbed DBT + SM (CC + MLO for both): Same acquisition as #1 but with the DBT images displayed as 6 mm thick slabs with an overlap of 3 mm (3DQuorum Smart Slices, Hologic).AI-aided navigation: Same as #1 but interpretation performed with an accompanying computer system for navigation and decision support.

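### The AI cut-off is set at the live round-1 recall rate and is not tied to the readers' operating point in the 200-exam study, so a difference between hybrid and human double reading may reflect threshold rather than performance

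*Protocol article*

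**What the plan says.** Protocol article, Data analysis, Reading strategies (text after the Fig. 2 caption):

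- The human data: "Twenty radiologists will evaluate 200 examinations of the first round with each of the different reading strategies". For each reading the study records lesion locations and scores, "and a recall/no recall decision, in addition to reading time".
- Radiologists' readings are paired at random to imitate double reading. In the hybrid version the AI takes one reader's place, and a radiologist arbitrates discrepancies.
- The AI score is dichotomised at "the operating point that would result in the same average recall rate as the screening radiologists in the first screening round of this trial". I read this as the cut-off at which the AI would recall that share of first-round screening exams.
- "Sensitivity and specificity of the final screening outcomes will be the endpoint of these studies".
- If selected, a strategy is applied to all second-round exams, and "The recall rate, breast cancer detection rate, PPV of recall, and interpretation time will be compared to the first evaluation of the second round". No AI cut-off is named for that step.

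Protocol article, Statistical analyses: "The recall rate in the first round is expected to be higher due to the first-round effect of a more sensitive screening test", to which the text adds radiologist learning and the lack of DBT priors. It continues: "The recall rate of the second round will estimate the long-term recall rate for DBT screening".

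**The concern.** Sensitivity and specificity depend on where each party draws its line. The AI's line comes from live screening. The radiologists' line is whatever they use in a reader study, where a recall has no consequence for a woman and the case mix is probably very different. They also read under four display strategies, each of which could move their operating point, while the AI has one stated cut-off. Nothing links the two lines, although the readers' decisions are recorded and the AI gives a probability score.

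If the lines differ, an AI exactly as good as the readers will look different from them. The comparison informs which double-reading method is judged best, and the Microsimulation modelling section simulates and costs the best strategy. The trial's primary endpoint is not affected.

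**Working it through.** The article gives no numerical result for this comparison, so there is no plan figure to reproduce. The check has four steps.

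**1. Is the 200-exam set likely to be enriched?** Programme detection rates in the Introduction are 6.9 and 7.9 per 1000. An unselected 200 would hold 200 × 0.0069 = 1.38 to 200 × 0.0079 = 1.58 cancers. A sensitivity endpoint on 1 or 2 cancers makes no sense, so enrichment is very probable. The article says so only for the other 200-exam set, used for AI selection: "The dataset will be assembled from first-round cases and will include both cancer and negative cases".

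**2. Does enrichment alone cause the problem?** No. Take an equal-variance binormal model with d = √2 × Φ⁻¹(AUC) and an assumed prevalence π = 0.007. The cut-off t for population recall r solves r = π[1 − Φ(t − d)] + (1 − π)[1 − Φ(t)]. For AUC 0.90 (d = 1.812) and r = 2.4%, t = 2.029, sensitivity is 0.414 and specificity 0.9788. In a set with an assumed 35% cancers the same cut-off recalls 0.35 × 0.414 + 0.65 × 0.0212 = 0.159. Raw recall rises from 2.4% to about 16%, but the threshold has not moved. Distortion needs readers to use a different threshold in the study. It also follows that any matching should use false positives among non-cancer exams, not raw recall.

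**3. What happens if the readers' threshold does differ?** Assumptions: AI and readers share one ROC curve (AUC 0.90 or 0.95); latent scores correlate 0.5; the AI is set at 2.4% recall (the 2019 DM rate in the Introduction) or 3.5% (assumed); readers in the study are set at a threshold equivalent to 5%, 10% or 20% population recall (assumed). If the first two reads agree, that is the result; otherwise a human arbiter decides. There were 1,000,000 draws per condition.

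One row in full (AUC 0.90, AI at 2.4%, t = 2.029; readers at 10%, t = 1.306): sensitivity is 0.724 for human-human and 0.630 for hybrid, a change of -0.094; specificity is 0.938 and 0.962, a change of +0.024.

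Hybrid minus human-human, sensitivity / specificity:

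| AUC | AI recall | Readers matched | Readers 5% | Readers 10% | Readers 20% |
|---|---|---|---|---|---|
| 0.90 | 2.4% | 0.000 / +0.0001 | -0.052 / +0.0066 | -0.094 / +0.0238 | -0.101 / +0.0646 |
| 0.90 | 3.5% | +0.001 / +0.0002 | -0.027 / +0.0040 | -0.074 / +0.0200 | -0.089 / +0.0612 |
| 0.95 | 2.4% | 0.000 / +0.0001 | -0.046 / +0.0065 | -0.063 / +0.0239 | -0.053 / +0.0653 |
| 0.95 | 3.5% | +0.001 / 0.0000 | -0.022 / +0.0034 | -0.048 / +0.0197 | -0.045 / +0.0613 |

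With matched thresholds the difference is simulation error. If readers were stricter in the study than live, the signs would reverse.

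**4. Which recall rate is meant?** The average could be that of individual readers, or the rate after arbitration, which is closer to how Statistical analyses defines recall (women recalled per 1000 screened). In the same model (AUC 0.90, readers at 2.4%), the single-reader false-positive rate is 1 − 0.9788 = 2.12%, against 1 − 0.9914 = 0.86% after arbitration. An AI that replaces one reader but is matched to the arbitrated rate would be markedly stricter than the reader it replaces.

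**Round 2.** At AUC 0.90, moving the AI from 2.4% to 3.5% recall moves its sensitivity from 0.41 to 0.48 and its specificity from 0.979 to 0.968. A round-1 cut-off therefore matters if round-1 recall is above the long-term rate, as the article expects.

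**The case against.** **A cut-off set in advance from real screening is a proper definition of the AI as it would be deployed.** This stands. Tuning the AI on the evaluation set uses the cancer status of the exams and imports any study behaviour of the readers. The planned cut-off should stay; the weakness is that it is the only one.

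**Threshold-free measures are already planned.** AUC and JAFROC are estimated for the reading strategies, AUC is computed for the AI on first-round data, and the Abstract names AUC and reading time for the best reading method. These help in interpretation. They do not repair the double-reading comparison, whose stated endpoint is sensitivity and specificity.

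**No figure shows that readers will shift.** This also stands. The article gives neither the cancer share of this set nor the readers' recall in it.

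Four stronger readings are tempting and are not supported:

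- *That the round-1 rate is not the readers' operating point in the set.* One can say only that it need not be.
- *That the raised first-round recall distorts the 200-exam comparison.* The exams and the rate come from the same round, so the elevation does not by itself distort it.
- *That threshold alone could produce 16 to 34 points of sensitivity.* At an assumed AUC of 0.93, single-reader sensitivity is 0.632 at a 4% and 0.790 at a 10% false-positive rate (difference 0.158), and 0.551 at 2.5% and 0.894 at 20% (difference 0.343). The endpoint is the outcome after arbitration, where both versions share a radiologist reader and a radiologist arbiter.
- *That a hybrid would be biased against in round 2 by construction.* This requires that a hybrid is selected and that the round-1 cut-off is carried over, which the article does not say. Two of its three reasons for higher first-round recall concern how radiologists read, extra AI flags go to arbitration, and detection is reported as well as recall.

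**Conclusion.** The concern holds in a limited form. The article fixes the AI's threshold from live screening, takes the human threshold from a reader study, and uses a threshold-dependent endpoint with nothing tying the two together. A difference between hybrid and human double reading then cannot be attributed to the AI's performance.

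Under the stated assumptions (shared ROC curve, AUC 0.90 or 0.95, latent correlation 0.5, readers laxer in the study), the spurious change is about -0.02 to -0.10 in sensitivity and +0.003 to +0.065 in specificity. It is nil if the readers keep their live threshold, and the article does not show which will occur. For round 2 the point is conditional: should a hybrid be taken forward, the article's own expectation of higher first-round recall makes the round-1 rate a poor sole basis for the cut-off. This is a secondary study, but the remedy is cheap and changes what the comparison can conclude.

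**What to change.** 1. Keep the round-1-recall cut-off as the as-deployed analysis.
2. Add a pre-specified analysis, for each of the four reading strategies, with the AI cut-off set so that its false-positive rate on the non-cancer exams equals the mean single-reader false-positive rate in the same 200 exams. Attribute a difference to the AI only if it persists there.
3. Define the recall rate used for matching as single-reader, before arbitration, because the AI replaces one reader.
4. If a hybrid strategy enters the round-2 re-read, fix its cut-off before reading starts and do not carry the round-1 cut-off forward as the only one. Also report results with AI recall matched to mean single-reader recall in the first evaluation of round 2.

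Cost: wording and extra analyses of AI scores and reader decisions that are collected anyway. Two thresholds must be reported. The matched cut-off is tuned on the evaluation set, and in round 2 matching partly predetermines the recall comparison, so the matched results are supportive and do not replace the as-deployed result. Matching will also be coarse: with an assumed 35% cancers there are 0.65 × 200 = 130 non-cancer exams, so the AI's false-positive rate moves in steps of 1/130, about 0.8 percentage points.

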### Incidental findings

In case a suspicion of breast cancer is identified during the reader study sessions in a participant who was not recalled for work-up, the study radiologists will consult with the coordinating radiologist from the reading unit to decide if recall of this woman is indicated. This protocol is comparable to the protocol used by BVO-NL in case a meeting of screening radiographers results in a suspicion of breast cancer in a participant not recalled.

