## Discussion

The major strength of STREAM is its prospective parallel-group design and its real-world evaluation of different reading strategies. To the best of our knowledge, no prospective trial has evaluated different reading methods for DBT on such a large cohort. This design will give insights into the implementation and acceptability of DBT in the population screening practice.

There are a few limitations to this trial. First, the reader study sessions will start after the first round of data is collected. At that moment, we will not yet have information on ICs. Therefore, the AI solutions will be evaluated on recall and breast cancer detection data from round 1 only. We will re-evaluate the AI solutions once round 2 is completed, but we cannot redo the reading strategy analysis in the funding period. The second evaluation will, therefore, only serve to check if there are significant differences in the results of the AI predictions. This could mean that if a reading strategy including AI is selected as optimal, that strategy does not consider the fact that the AI could be detecting ICs that have not been detected yet. This in turn might influence the evaluation of normal reading versus optimal reading strategy.

Furthermore, in the first round of this trial, there are no previous DBT images available to compare against the current case. Instead, the radiologists are provided with the previous mammogram. Therefore, the first round does not really reflect the possible future steady state in which all priors would consist of DBT images. The second round will have previous DBT images available and will reflect the future steady state more accurately.

The results from the STREAM trial will indicate whether it is beneficial to implement DBT screening in the Netherlands by looking at short-, medium-, and long-term effects, optimal reading strategies, cost-effectiveness, and the acceptability of various stakeholders. In addition, these results will be relevant for other countries considering implementing DBT in screening.

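### The second-round re-reading uses the first readers' decision as both comparator and gold standard, so the chosen strategy's detection rate cannot exceed theirs and its PPV is understated

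*Protocol article*

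**What the plan says.** The protocol article, Reading strategies, last paragraph (after Fig. 2), sets out the full-cohort evaluation of the chosen strategy: "Once the best reading strategy has been found, all DBT examinations of the second round will be re-interpreted using it". The reference is fixed next: "The decision of the first evaluation by the two radiologists will be the gold standard". The outcomes follow: "The recall rate, breast cancer detection rate, PPV of recall, and interpretation time will be compared to the first evaluation of the second round". The chosen strategy may be one in which AI replaces a reader.

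Three other places bear on this:

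- **Statistical analyses.** Detection rate counts women with screen-detected cancer, and PPV is the share of recalled women with such a cancer. Data on screen-detected and interval cancers "will be obtained through linkage with the Netherlands Cancer Registry and the Dutch nationwide pathology databank". Interval cancers are counted "in the first, second, and third year after the first screening round of the trial per 1000 screens". No window after the second round is given.
- **Incidental findings.** A consultation on recall is foreseen "In case a suspicion of breast cancer is identified during the reader study sessions in a participant who was not recalled for work-up".
- **Discussion.** If a strategy with AI is selected, the authors concede "that strategy does not consider the fact that the AI could be detecting ICs that have not been detected yet". The context is selection on first-round data.

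**The concern.** A reading method cannot do better than its comparator when the comparator also decides which women have cancer. The re-reading can lose cancers that the first two radiologists found, but it cannot gain any that they missed. Yet finding missed cancers is one of the ways in which a new strategy, especially one with AI, could be better.

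The other reader comparisons use sets of 200 examinations. The second-round re-reading is the only evaluation of the chosen strategy on the whole cohort, and the article presents it as a test under real screening conditions. Under Microsimulation modelling, the trial and reading-strategy results feed the MISCAN-Breast model and the cost-effectiveness analysis. A detection rate biased in one direction could therefore carry into the advice on implementation.

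**Working it through.** **1. The set to be re-read.** Sample size calculations states: "This requires a sample size for the intervention group in the second round of 17,275 screening examinations with DBT". Inputs there: 3.6 per 1000 with DM, a reduction of 1.3 (so 2.3 with DBT), two-sided alpha 0.05, power 0.80, ratio 5. With pooled variance and no continuity correction, and p̄ = (0.0023 + 5 × 0.0036)/6 = 0.003383:

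n = [1.960 × √(p̄(1 − p̄) × 1.2) + 0.8416 × √(0.0023 × 0.9977 + 0.0036 × 0.9964/5)]² / 0.0013² = (0.12467 + 0.04619)² / 0.00000169 ≈ 17,275.

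The plan's figure is reproduced. The article gives no figure for the re-reading itself, so the rest is logic plus illustration.

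**2. Does the cap depend on how the sentence is read?**

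- *Literal reading: the recall decision is the truth.* A woman not recalled at first evaluation is then a non-case. The re-reading cannot gain.
- *Middle reading: the truth is cancer diagnosed after a first-evaluation recall.* A missed cancer is not in the numerator. The re-reading cannot gain.
- *Loose reading: gold standard only means comparator.* Detection still counts screen-detected cancers. A cancer missed at first evaluation and found clinically later would be an interval cancer, and the article defines those only after round 1. No reference is named for women flagged only at re-reading, so the re-reading still cannot gain.

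**3. Ceiling.** Programme detection rates from the Introduction are 6.9 per 1000 (2019) and 7.9 per 1000 (2022):

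- 17,275 × 6.9/1000 = 119.2
- 17,275 × 7.9/1000 = 136.5

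The re-reading can be credited with at most about 119 to 136 cancers, if second-round DBT detects at these rates (an assumption).

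**4. Paired test with the gain cell at zero.** The article names no paired test here; I use the exact McNemar test. With c cancers lost and none gained, two-sided p = 2 × 0.5^c:

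- c = 5: p = 0.063
- c = 6: p = 0.031

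A loss of 6 is 6/136 = 4.4% to 6/119 = 5.0% of the first-read cancers. Better detection cannot be shown at any sample size.

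**5. Effect on the detection rate.** Assumptions, none of them in the documents: the strategy keeps 95% of first-read cancers; missed cancers number 1.0 to 2.3 per 1000 (17 to 40 women); half of these are flagged at re-reading.

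| First evaluation, per 1000 | Re-read as written | Re-read with missed cancers ascertained |
|---|---|---|
| 6.9 | 0.95 × 6.9 = 6.6 | 6.555 + 0.5 to 1.15 = 7.1 to 7.7 |
| 7.9 | 0.95 × 7.9 = 7.5 | 7.505 + 0.5 to 1.15 = 8.0 to 8.7 |

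Under these assumptions an apparent loss becomes a gain. If only a quarter are flagged, the first row becomes 6.8 to 7.1 and the second 7.8 to 8.1, so the sign then depends on the missed-cancer rate.

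**6. PPV.** At the programme's 2.4% recall, 17,275 × 0.024 = 415 women are recalled. With 119 cancers, PPV is 119/415 = 28.7%. Suppose the re-reading recalls 350 women and keeps 113 of the 119: the credited PPV is 113/350 = 32.3%. If 10 of the remaining 237 women have missed cancers, the true figure is 123/350 = 35.1%. PPV is understated, but it can still favour the new strategy.

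**The case against.** The strongest reply is that the sentence is loosely worded. If a recall decision were literally cancer status, the first evaluation's PPV would be 100% and its detection rate would equal its recall rate, which conflicts with the definitions under Statistical analyses. This stands as far as it goes: the article does not say how women flagged only at re-reading are scored. A reader might infer that they are false positives by rule, but that is an inference. It does not remove the cap, because step 2 of the working reaches the same result on the loose reading.

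A reader might also infer that the evaluation can only make the new strategy look equal or worse overall. The documents do not support that. Interpretation time, which is the main motive for optimising reading, and recall rate do not depend on cancer status, and PPV can improve if false recalls fall. Only detection is capped.

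The Incidental findings section could bring some missed cancers to work-up. It speaks of reader study sessions, however, and whether the second-round re-reading is covered is unclear. Recall there depends on a consultation, and nothing says such cancers count as detections. So one cannot say that no missed cancer would ever be diagnosed, only that the stated reference gives no credit for it.

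The limitation in the Discussion recognises a related mechanism and says it might affect the comparison of normal with optimal reading. It concerns choosing the strategy on first-round data, not the second-round reference.

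Finally, the missed-cancer rate and the share flagged are assumptions. They affect the size of the bias, not its direction.

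**Conclusion.** The point holds for detection rate and PPV in the second-round re-reading. As written, the detection difference can only be zero or negative, and cancers flagged only at re-reading enter the recalls without entering the cancers. The size is unknown because the number of missed cancers is unknown. At 6.9 to 7.9 per 1000 the ceiling is about 119 to 136 cancers, and a net loss of 6 would already reach p = 0.031 while no gain can be recorded.

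Recall rate, interpretation time, the DBT-versus-DM comparison, the primary endpoint and the sample size are untouched. This should be fixed before the re-reading is analysed, but it does not threaten the trial's main conclusion.

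**What to change.** Replace the gold-standard sentence along these lines: the first evaluation is the comparator; cancer status for both readings is defined by registry- and pathology-linked diagnosis. It comprises (a) cancers diagnosed after second-round recall, (b) cancers found by any work-up prompted by the re-reading, and (c) interval cancers in a fixed window, for example 12 months, after the second-round screen. Item (b) is needed because such cancers are neither (a) nor (c). Compare the readings as paired data on the same examinations, and report women flagged only at re-reading as unverified until linkage.

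**Cost.** This is more than wording. A reader might assume that the planned linkage already covers it, but the interval-cancer definition stops at the period after round 1, so follow-up must be extended. Inclusion ended in May 2024. With a two-year interval, round 2 ends around mid-2026 and a 12-month window around mid-2027. With the 32-month interval mentioned in the Introduction, the dates are about January 2027 and January 2028, leaving some four to five months before the licence ends on 1 June 2028. Registry delay is not stated. The change is feasible but tight, and it delays the final comparison.

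**Fallback.** If the follow-up is not available in time, report the re-read detection rate and PPV as lower bounds, draw no conclusion of inferior detection from them, carry that label into the microsimulation, and rest the claim on agreement, recall rate and interpretation time.
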